#### 8.1.1 OS and PFS

All statistical tests for the efficacy endpoint OS and PFS will be performed according to intention-to-treat (ITT) principle, which is the most unbiased method. Considering the trial being a non-inferiority trial, which is more sensitive to bias, a secondary per-protocol (PP) analysis will be done for OS [43]. The PP analyses will be performed on a “subset of patients who complied sufficiently with the protocol, such as exposure to treatment, availability of measures and absence of major protocol violations” according to the ICH E9 guidelines. The ITT analysis includes all participants. Start date of ReRT will be used as time is 0. Patients not known to have died during the study will be censored for OS at the day they were last known to be alive. Patients free from progression and alive at the last visit will be censored for PFS at the day of last assessment. Endpoints are measured from the first date of re-irradiation.

Distributions of OS and PFS will be estimated by the Kaplan-Meier method. The OS rates at one year, PFS rates at six months and medians of OS and PFS will be presented with two-sided 95% confidence interval(CI) computed using the log-log transformation.

To minimize the effect of confounding when estimating the difference between the treatment and retrospective control group, stabilized inverse probability of treatment weighting (SIPTW) using propensity scores will be applied when comparing the groups on OS and PFS.

Propensity scores will be estimated using logistic regression including important covariates for OS and PFS: primary histology, GTV, KPS and age.

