### 4.2 Inclusion criteria

In order to be eligible to participate in study arm 1 and 2, a subject must meet all of the following criteria:

- Supratentorial recurrent high-grade glioma with contrast enhancement on CE-T1.
- The gold standard is histological evidence of a recurrence. When a surgical procedure to acquire this evidence is not desirable or possible, a recurrence may be diagnosed by radiological imaging alone, taking the following in consideration:
  - Agreement of the tumor board or a consultant neuro-radiologist that imaging changes are in keeping with recurrence.
  - An interval of no less than 3 months since last (chemo)radiotherapy.

- Utilization of the RANO criteria for tumor progression [29].
- If needed, additional imaging sequences such as PET and perfusion MRI.
- Unifocal glioma (i.e. lesions clustering around residual surgical cavity).
- Prior course of treatment including radiotherapy with an EQD2 ( $\alpha/\beta = 2$ ) of at least 47Gy.
- Age  $\geq 18$  years.
- Karnofsky Performance Score 60 or above.
- Ability of subject to understand character and individual consequences of the clinical trial (arm 1).
- Patients who received re-irradiation for the recurrence of a primary brain tumor with a treatment schedule of 10x3.5Gy (arm 2).

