#### 6.1.2 Secondary study parameters/endpoints

The key secondary endpoint is:

- Progression free survival (PFS) counted from the first date of re-irradiation until the date of MRI evidence of tumor recurrence or death due to any cause. Agreement of the tumor board or a consultant neuro-radiologist that imaging changes are in keeping with recurrence and not radionecrosis is necessary.

Other secondary endpoints include the following:

- Recurrence Patterns on MRI.
- Radiation toxicity graded by CTCAE v5.0
- Anti-edema therapy (including Dexamethasone and Bevacizumab use).
- Health Related Quality of Life (HRQoL) prospectively monitored by EQ-5D-5L, EORTC QLQ-C15-PAL and EORTC-QLQ-BN20+2 questionnaires. (only for the experimental arm 1, cannot be analyzed retrospectively in the control arm 2).

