**Table 3. Treatment and follow-up procedures per patient in experimental arm 1**

|                                     | Baseline | Treatment and follow-up period (weeks after first fraction) |   |   |    |    |    |    |
|-------------------------------------|----------|-------------------------------------------------------------|---|---|----|----|----|----|
|                                     |          | 2                                                           | 4 | 6 | 13 | 26 | 39 | 52 |
| Baseline characteristics and intake | X        |                                                             |   |   |    |    |    |    |
| Hypofractionated RT                 |          | X                                                           |   |   |    |    |    |    |
| HRQoL                               | X        | X                                                           | X | X | X  | X  | X  | X  |
| Molecular analysis                  | X        |                                                             |   |   |    |    |    |    |
| Upload information/imaging          | X        |                                                             |   |   |    | X  |    | X  |

### 6.3 Study procedures retrospective Arm 2

The available data for the retrospective control group (arm 2) will be selected from the retro-RISinG trial.

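### PFS is dated to MRI scans whose interval is stated for neither arm, so a difference in scan timing alone could show up as a difference in PFS

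*Protocol*

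**What the plan says.** Protocol 6.1.2 makes PFS the key secondary endpoint, counted from the first day of re-irradiation "until the date of MRI evidence of tumor recurrence or death due to any cause". It adds a confirmation step: "Agreement of the tumor board or a consultant neuro-radiologist that imaging changes are in keeping with recurrence and not radionecrosis is necessary". Section 8.1.1.2 makes a two-sided 5% log-rank test the primary PFS comparison and adds a Cox hazard ratio. Section 8.1.1 plans estimates that include "The OS rates at one year, PFS rates at six months and medians of OS and PFS". On censoring it says: "Patients free from progression and alive at the last visit will be censored for PFS at the day of last assessment".

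Section 8.1.1 adjusts the comparison by stabilised inverse probability weights built from primary histology, GTV, KPS and age.

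No MRI interval is given for either arm. For arm 1, the Summary describes MRI as acquired in standard care, and section 9.3 limits hospital visits to standard follow-up. Table 3 has no MRI row, only one named "Upload information/imaging", marked at baseline and weeks 26 and 52. Section 8.3 takes for granted an MRI at six months. For arm 2, section 6.3 says: "The available data for the retrospective control group (arm 2) will be selected from the retro-RISinG trial". Section 4.1 puts 16 controls from RISING trial A and 83 from the registry, which covers January 2002 to December 2022.

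**The concern.** A progression that occurs between two scans is dated to the later one. If both arms are scanned on the same calendar, the delay is shared and the comparison stays fair. If one arm is scanned less often, its progressions are recorded later and its PFS looks longer, although nothing about the disease differs. Nothing in the protocol holds the scan calendar equal between a prospective cohort and a registry spanning two decades. The weights cannot do so, because scan frequency is not a baseline covariate in the propensity model.

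The six-month rate is a second exposure. A scan is expected at about six months, so a progression first seen on a scan a few days after the landmark counts as progression-free at the landmark.

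At stake is a significant PFS result, in either direction, produced by follow-up habits.

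**Working it through.** **Arm sizes.** The protocol gives no sample size or power for PFS, so the arm sizes come from the OS calculation in 4.4, which reproduces: events = (1.645 + 0.842)² / (0.4 × 0.6 × ln(1.4/0.9)²) = 6.183 / (0.24 × 0.1952) = 132; 132 / 0.80 = 165, split 66 and 99. The registry share of controls is 83/99 = 84%.

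**First simulation: no true difference.** Assumptions not in the protocol: exponential time to progression with median 4-6 months, independent exponential death with median 9 months (inside the 7.7-11.5 months quoted in 1.1), scans jittered by ±2 weeks, progression dated at the next scan, no censoring, unweighted test. A 5-month median to progression with a 9-month median to death gives a median PFS of 5 × 9 / (5 + 9) = 3.2 months. Arm 1 is scanned every 13 weeks. Hazard ratios cover medians of 4-6 months; rejection rates use the 5-month median, 66 v 99 patients, and span repeat runs.

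| Control scan interval | Expected HR (true value 1) | Rejection by nominal 5% log-rank |
|---|---|---|
| 13 weeks | 1 | about 5% |
| 8 weeks | 0.92-0.94 | 7-10% |
| 18 weeks | 1.08-1.14 | 9-10% |
| 26 weeks | 1.17-1.28 | 25-26% |

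More frequent scanning of controls flatters the experimental arm; less frequent scanning does the reverse.

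**Second simulation: other assumptions.** Median PFS 3 to 6 months, 20% of events deaths without progression, jitter ±1 week, follow-up 52 to 182 weeks, arm 1 every 13 weeks. Results run from the 3-month to the 6-month median:
- Controls every 6.5 weeks: HR 0.86 to 0.93, rejection 16% to 6%.
- Controls every 8 weeks: HR 0.90 to 0.95, rejection 11% to 5%.
- Controls every 17 weeks: HR 1.15 to 1.07, rejection 16% to 8%.
- Controls also every 13 weeks: HR 1.00, rejection 4.7% to 6.6%.

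**Six-month rate.** Six months is 365.25/2 = 182.6 days; 26 weeks is 182 days. Under the first set of assumptions the true six-month PFS is 2^−(6/4 + 6/9) = 22% to 2^−(6/6 + 6/9) = 32%. With 13-week scans the observed rate is 30-38%, which is 7-8 points too high; with 8-week scans the excess is about 2 points. Under the second set, if both arms are scanned every 13 weeks but arm 1 scans run 0-2 weeks late and control scans 0-2 weeks early, the six-month rates are 0.42 v 0.26 (3-month median) to 0.65 v 0.51 (6-month median), a false gap of 14-16 points.

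**Censoring.** Under the second set, with the same 13-week scans in both arms, censoring arm 1 at a visit or phone date and controls at the last scan gives HR 0.99 and rejection of 5-6%. When follow-up is complete to one year the effect is negligible.

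**The case against.** The strongest reply is that no document shows the intervals to differ. Arm 1 is not on a research scan calendar: its imaging is standard care, as the registry's was, and 16 controls come from the randomised trial A. The 25% figure needs half-yearly scans in a disease with a quoted median survival of 7.7-11.5 months. At nearer intervals the distortion is modest. This stands, and it limits the claim to a risk of unknown direction. It does not remove the risk: standard care is not shown to have been the same in 2002 as now, and the protocol has no means of finding out.

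A second reply is that such detail belongs in the SAP. That is fair for the exact meaning of the last assessment. But the event date, the landmark and the primary test are already fixed in the protocol, and a later plan can correct for scan timing only if scan dates, including those of negative scans, are collected in both arms. The protocol does not ask for them.

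Third, the six-month rate is presented with a confidence interval and not tested, and with equal scanning its excess affects both arms alike. This also stands. The rate is misleading between arms only if timing differs, and as an absolute figure whenever scans are sparse.

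Several stronger readings are tempting but not supported:
- A reader might infer that unscanned time counts as progression-free in arm 1 only. Control charts may also hold visits without MRI, the arm 1 phone calls collect quality of life, toxicity and anti-edema treatment and not progression, and the numerical effect is negligible.
- A reader might take week 26 in Table 3 as a scheduled scan. It is an upload point; the six-month MRI rests on section 8.3.
- A reader might hold that the endpoint lacks criteria because RANO is named only at entry ("Utilization of the RANO criteria for tumor progression"). Section 6.1.2 already requires expert agreement that excludes radionecrosis.

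**Conclusion.** The concern holds for the key secondary endpoint as a risk the protocol leaves unguarded. With no true difference, a 5-month median time to progression and arm 1 scanned every 13 weeks, the 5% log-rank test rejects in about 7-10% of trials at control intervals of 8 or 18 weeks and about 25% at the extreme of 26 weeks. The second set of assumptions gives 5-11% at 8 weeks and 8-16% at 17 weeks. All scan intervals, the time-to-progression distribution and the jitter are assumptions; the protocol supplies none of them. The simulations used an unweighted test. The direction cannot be known in advance, so a reader should not infer that the plan favours the 4-fraction arm. The six-month rate shares the sensitivity. The ambiguity over the last assessment needs clarifying but does not drive the result. The primary endpoint, OS, is unaffected.

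**What to change.** In Protocol 8.1.1:
1. Record the date and result of every MRI after re-irradiation in both arms, negative scans included, and report the scan intervals by arm.
2. Beside the planned log-rank test and Cox model, pre-specify a sensitivity analysis of PFS with progression interval-censored between the last negative and the first positive MRI, using the planned propensity weights.
3. State that, for PFS, the last assessment means the last MRI without progression, in both arms.
4. Give the six-month PFS rate from the interval-censored estimate as well as from Kaplan-Meier.

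Moving the landmark is not a reliable substitute. Read at 30 weeks, 13-week scans still give 21-30% against a true 18-27%, and with 8-week scans the excess grows from about 2 to 4-5 points. Replacing the log-rank test as the primary PFS comparison is not needed.

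No additional scan is needed. The cost is wording, extraction of scan dates and somewhat wider intervals. The protocol does not say that the registry already holds every scan date, but imaging has to be retrieved in both arms anyway to compare recurrence patterns (2.2 and 8.1.2).

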### 3. STUDY DESIGN

The original 2019 RISING-trial (RISING trial A) was designed as an open label, randomized, non-inferiority, phase III trial with 1:1 allocation for 130 patients. In this trial 13 patients were included in the experimental arm and 16 patients were included in the control arm. The updated 2023 RISinG trial (RISING trial B) is designed as a phase II, multi-center, clinical trial with a historic control group. The additional recruitment period of this phase will be approximately 30 months with an active follow-up time of 12 months.

The 13 patients of the RISING trial A will be supplemented until a total of 66 patients is reached. These patients fulfilling the inclusion criteria will get the following treatment:

- Hypofractionated radiotherapy with SIB in 2 weeks  
4 fractions of 7.5 Gy SIB to the GTV  
And 4 fractions of 5.5 Gy to the CTV (GTV + 5mm margin).

We will compare the survival of this group with a retrospective control group of patients, subtracted from the retro-RISinG registry study, a multi-center retrospective nation-wide population based cohort study, in which details of patient-, tumor- and treatment-related data of all patients with a recurrence of a primary brain tumor since January 2002 up to December 2022 in the Netherlands will be collected. We will select 99 matched patients in total with the following treatment:

- Moderately hypofractionated radiotherapy in 2-3 weeks  
10 fractions of 3.5 Gy to the CTV (GTV + 5 mm margin)

An overview of the target volume definitions and dose prescriptions is presented in table A3 in section 1.8 of the Appendix.

This control group will be matched to the patients in the experimental arm on an individual level for:

1. Age;
2. Gender;
3. WHO-grade primary tumor;
4. Time interval in between first radiation and re-irradiation;
5. MGMT-status.

[figure not shown]

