##### 8.1.1.1. OS

The hazard rate for the experimental versus the retrospective control group and its two-sided 80 and 95% CIs will be estimated using a Cox proportional hazards model. We will adjust for confounding using propensity scores.. Omission of 4 fractions as non-inferior to 10 fractions of radiotherapy if the higher 90% CI of the hazard ratio (HR) of 4 fractions versus 10 fractions was not above 1.4.

Only when non-inferiority has been demonstrated, we will test for superiority of the experimental treatment in a hierarchical fashion, using Kaplan-Meier method and two-sided log-rank test at a significance level  $\alpha = 10\%$  in ITT analysis.

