### **8.1.5 Prognostic and predictive factors**

Additional exploratory analyses using Cox regression analyses will study the prognostic impact of factors (other than treatment, age, gender, WHO-grade primary tumor, time interval in between first radiation and re-irradiation and MGMT-status), including baseline KPS, number of recurrence, tumor volume and dexamethasone use at baseline. In addition, the predictive value for the treatment effect of the 4 and 10 fraction regimens of these factors will be investigated using Cox Regression analyses.

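### The propensity model leaves out gender, re-irradiation interval and MGMT, and possibly WHO grade, on which controls are matched, so weighting no longer guarantees their balance

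*Protocol*

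**What the plan says.** Section 3 introduces the matching with "This control group will be matched to the patients in the experimental arm on an individual level for" and lists five factors: age, gender, "WHO-grade primary tumor", "Time interval in between first radiation and re-irradiation" and MGMT status.

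Section 8.1.1 states that "stabilized inverse probability of treatment weighting (SIPTW) using propensity scores will be applied when comparing the groups on OS and PFS". It fixes the model behind those weights: "Propensity scores will be estimated using logistic regression including important covariates for OS and PFS: primary histology, GTV, KPS and age".

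Section 8.1.1.1, on the primary Cox model, says only "We will adjust for confounding using propensity scores". It names no matched sets, strata or further covariates. The log-rank tests for OS superiority (8.1.1.1) and PFS (8.1.1.2) are described without mention of weights.

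Section 8.1.5 explores prognostic factors "other than treatment, age, gender, WHO-grade primary tumor, time interval in between first radiation and re-irradiation and MGMT-status". The five matching factors are thus set apart as already dealt with.

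On which controls are matched, section 3 speaks of 99 matched patients in total. Section 4.1 counts 16 controls from trial A and 83 further registry patients, and describes the matching when it introduces the latter.

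**The concern.** Individual matching makes the arms alike on the five factors only while each patient counts as matched. Inverse probability weights give those patients unequal weight, according to a model that does not contain most of these factors. If KPS or GTV differs between arms and is related to, say, the interval, weighting that removes the KPS or GTV difference also moves the interval, and nothing in the model pulls it back.

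The protocol itself treats these factors as relevant. Both cohort studies summarised in section 1.1 adjusted for time interval and initial WHO grade, and section 1.4 describes MGMT as bearing on outcome. Most controls are not randomised, so the comparison with the 1.4 margin depends on confounding control. A residual imbalance in a prognostic factor passes directly into the hazard ratio.

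**Working it through.** **The two lists side by side**

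| Factor | Matched (section 3) | In propensity model (8.1.1) |
|---|---|---|
| Age | yes | yes |
| Gender | yes | no |
| WHO grade of primary tumor | yes | not named; overlap with histology undefined |
| Interval to re-irradiation | yes | no |
| MGMT | yes | no |
| Primary histology | not named | yes |
| GTV | no | yes |
| KPS | no | yes |

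Only age is named in both.

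**The plan's own sample size.** Inputs from section 4.4: one-sided alpha 0.05, power 0.80, true HR 0.90, margin 1.4, allocation 40:60, event proportion 0.8.

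Events = (1.645 + 0.842)² / (0.4 × 0.6 × [ln(1.4/0.9)]²) = 131.96, so 132. Patients = 132 / 0.8 = 165. The stated figure reproduces.

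The standard error of the log HR is 1/√(132 × 0.24) = 0.1777.

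**How far weighting can move a matched factor.** Simulation with 66 experimental patients and 99 controls. Factor X is balanced by matching and covariate Z stands in for KPS or GTV. Stabilised weights come from a logistic model on Z alone, then on Z and X. The correlations and arm differences are assumptions; the protocol gives neither.

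| Correlation of X and Z | Arm difference in Z (SD) | Mean drift of X, X omitted (SD) |
|---|---|---|
| 0 | 0.3 to 0.5 | about 0 |
| 0.2 | 0 | about 0 |
| 0.2 | 0.3 | 0.06 |
| 0.2 | 0.5 | 0.10 |
| 0.3 | 0.3 | 0.09 |
| 0.3 | 0.5 | 0.16 |

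With X in the model, the mean drift is within 0.005 of zero in every setting.

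**Effect on the non-inferiority test.** Assume X carries an HR of 0.70 per SD, so ln(1/0.70) = 0.357. Then:

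- bias on the log HR = drift × 0.357
- type I error at true HR 1.4, bias favouring 4 fractions = Φ(bias/0.1777 − 1.645)
- power at true HR 0.90, bias against 4 fractions = Φ((ln(1.4/0.9) − bias)/0.1777 − 1.645)

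| Drift (SD) | Bias on log HR | Type I error | Power if bias goes the other way |
|---|---|---|---|
| 0 | 0 | 5.0% | 80% |
| 0.06 | 0.021 | 6.4% | 76% |
| 0.092 | 0.033 | 7.2% | 74% |
| 0.157 | 0.056 | 9.2% | 70% |

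These rows take the loss of information from weighting as nil. In these settings the effective sample size was 0.92 to 0.97 of nominal when the arm difference in Z was 0.3 to 0.5 SD, and practically the same whether or not X was in the model.

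**The case against.** The design has a sensible logic: match on some factors, then weight on those that could not be matched, KPS and GTV. A final statistical analysis plan is also foreseen in section 8.1. The logic stands, but it needs the matching factors carried forward into the weighted model, and that is not done. The later plan does not settle the matter, because the protocol itself fixes both lists and foresees only minor revisions.

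Several stronger readings are tempting and are not supported:

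- **Four of the five matching factors are ignored.** That is true by name only. Primary histology may carry much of the WHO grade; the protocol does not say. Three omissions are certain.
- **Weighting destroys the matched balance.** It removes the guarantee. Mean drift is near zero if GTV and KPS are balanced or unrelated to the matched factors, and the protocol gives no data on either condition. The simulation also uses one factor and one covariate, so it illustrates the mechanism and does not forecast the result for each factor.
- **The 16 trial A controls are unmatched and uncontrolled.** Sections 3 and 4.1 can be read either way. Those 16 were randomised alongside the 13 experimental patients of trial A, which gives partial protection, though not against the other 53 (66 − 13) patients in arm 1.
- **The registry's span inflates the error further.** Controls come from a registry with data "since January 2002 up to December 2022 in the Netherlands will be collected", and calendar year is in neither list. A survival trend over time would be a separate problem: the protocol gives no size for one, and adding the matching factors to the model would not remove it. It is not counted here.

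**Conclusion.** The point holds as a mismatch between two lists that the protocol itself fixes. Gender, interval and MGMT, and WHO grade unless histology includes it, are not protected in the weighted primary analysis. That much rests on the text alone.

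The size is much less certain. It runs from no effect to a one-sided type I error of about 9% at the 1.4 margin, or a fall in power to about 70% if the bias runs against 4 fractions. The non-zero figures, from about 6% upward, rest on assumed correlations of 0.2 to 0.3, assumed arm differences of 0.3 to 0.5 SD in KPS or GTV, and an assumed HR of 0.70 per SD. The direction cannot be known in advance. The case for changing the plan is that the correction is cheap and removes the mechanism, not that a large bias has been shown.

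**What to change.** 1. In section 8.1.1, fit the propensity model on the union of both lists: age, gender, WHO grade and primary histology, interval between first radiation and re-irradiation, MGMT, GTV and KPS.
2. Report weighted standardised differences between arms for all of these factors.
3. State in sections 8.1.1.1 and 8.1.1.2 that the OS superiority and PFS log-rank tests use the same weights as the Cox models.
4. Reconcile sections 3 and 4.1 on whether the 16 trial A controls are matched to arm 1 or only the 83 registry patients are.

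The cost is a few more model terms, all on variables already needed for the matching or the present model, and slightly more variable weights. The sample size calculation stays at 132 events and 165 patients. The change should be made before outcomes are analysed.

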### 4.3 Exclusion criteria

A potential subject who meets any of the following criteria will be excluded from participation in this study (arm 1 and 2):

- Previous re-irradiation or prior radiosurgery or prior treatment with interstitial radioactive seeds.
- CE-T1 tumor diameter greater than 6cm ( reflecting a spherical tumor of 125cc).
- Time interval of less than 6 months after prior radiotherapy.
- Time interval of less than 3 weeks after last re-resection (1 week for biopsy).
- Known carcinoma < 3 years ago (excluding Carcinoma in situ of the cervix, basal cell carcinoma, squamous cell carcinoma of the skin) requiring immediate treatment interfering with study therapy.
- Women with childbearing potential without adequate contraception.

If a patient is not eligible for arm 1 based on the MRI results (e.g. T1-CE diameter >6 cm, reflecting a spherical tumor of 125 cc), these non-eligible patients are being replaced by new patients. These non-eligible patients are not included in the statistical analysis of the trial and treated with the physicians' choice.

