### 5.4 Use of co-intervention

Concomitant dexamethasone and anticonvulsant therapy is allowed. Salvage surgery prior to start radiation is allowed. Systemic therapy including chemotherapy, immunotherapy or targeted therapy during ReRT is not allowed.

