##### 1.3.1 Gross Tumour Volume (GTV)

The GTV is defined as the contrast enhancing lesion on CE-T1 MRI sequence for both treatment groups. GTV can be expanded using the other clinically acquired MRI sequences according to the expertise of the local radiation oncologist and the medical team.

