## **1.7 Timing of radiotherapy**

The interval between the planning-MRI and actual first fraction of ReRT is 3 weeks at most.

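### Salvage re-resection before re-irradiation is allowed, yet it is in neither the matching nor the propensity model, and GTV is only an incomplete proxy for it

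*Protocol*

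**What the plan says.** **Surgery is permitted before time zero.** Protocol section 5.4 states: "Salvage surgery prior to start radiation is allowed". Section 1.1 names re-resection beside chemotherapy and ReRT as a salvage option.

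**Recent surgery must be checked in both arms.** Section 4.3 opens with "A potential subject who meets any of the following criteria will be excluded from participation in this study (arm 1 and 2") and lists "Time interval of less than 3 weeks after last re-resection (1 week for biopsy").

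**Matching.** Section 3 says "This control group will be matched to the patients in the experimental arm on an individual level for" five items: age, gender, WHO grade of the primary tumor, interval between first radiation and ReRT, and MGMT status.

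**Propensity weighting.** Section 8.1.1 fixes the list: "Propensity scores will be estimated using logistic regression including important covariates for OS and PFS: primary histology, GTV, KPS and age".

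**Exploratory factors.** Section 8.1.5 adds a Cox analysis of further factors, "including baseline KPS, number of recurrence, tumor volume and dexamethasone use at baseline".

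Re-resection is in none of these three lists.

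**GTV.** Appendix 1.3.1 says: "The GTV is defined as the contrast enhancing lesion on CE-T1 MRI sequence for both treatment groups". Appendix 1.7, in the arm 1 radiotherapy protocol, adds: "The interval between the planning-MRI and actual first fraction of ReRT is 3 weeks at most".

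**Controls.** By section 4.1, 16 of the 99 controls come from the randomized trial A and 83 from a national registry covering January 2002 to December 2022.

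**The concern.** For 83 of the 99 controls there is no randomization, so matching and weighting are the main protection for the primary non-inferiority claim. Section 8.1.1 itself notes that a non-inferiority comparison is more sensitive to bias. Re-resection is a salvage treatment given before time zero (the start of ReRT), and its use may well differ between a current prospective arm and controls treated over two decades. If it affects survival, an imbalance enters the hazard ratio as though it were an effect of the 4-fraction schedule.

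GTV does not close this gap. An operated patient with a small enhancing residual and an unoperated patient with a small recurrence can have the same GTV, and the model then treats them as alike. GTV would stand in fully for surgery only if surgery acted on survival solely through residual volume. Selection for surgery, tumor location and preoperative extent are not in the model, and KPS reflects fitness only in part.

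**Working it through.** **Step 1. The plan's own sample size.** Inputs from section 4.4: one-sided alpha 0.05, power 0.80, true HR 0.90, margin 1.4, allocation 40:60, event proportion 0.8.

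- Events = (1.645 + 0.842)² / (0.4 × 0.6 × [ln(1.4/0.9)]²) = 6.183 / (0.24 × 0.4418²) = 131.96, rounded up to 132.
- N = 132 / 0.8 = 165, which agrees with the protocol (99 + 66).
- SE of log HR = 1/√(132 × 0.24) = 0.1777.
- Non-inferiority then needs an observed HR of at most 1.4 × exp(−1.645 × 0.1777) = 1.045.

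**Step 2. Does GTV measure the residual?** The 3-week exclusion does not name its end point; I take it to be the start of ReRT. An eligible patient's last re-resection is then at least 3 weeks before the first fraction. The arm 1 planning MRI is at most 3 weeks before it, so the MRI falls at or after any permitted re-resection. In arm 1, GTV is therefore the postoperative enhancing residual. For arm 2 the GTV definition is given but the timing of the MRI is not.

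**Step 3. Possible size of bias.** The documents give no re-resection share and no effect on survival, so everything here is assumed. Let a and c be the re-resected shares in arm 1 and the controls, and h the HR for death in re-resected patients.

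- Bias factor f = (1 − a(1 − h)) / (1 − c(1 − h)).
- Probability of declaring non-inferiority at true HR 1.4 = 1 − Φ(1.645 + ln f / 0.1777).
- Power at true HR 0.90 = Φ((0.4418 − ln f)/0.1777 − 1.645).

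For example, 30% vs 15% with h = 0.7 gives f = 0.910/0.955 = 0.953, ln f / 0.1777 = −0.272, and 1 − Φ(1.373) = 8.5%. For 40% vs 15% with h = 0.6, f = 0.84/0.94 = 0.894.

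| Assumed share, arm 1 vs controls | h | f | False non-inferiority at HR 1.4 | Power at HR 0.90 |
|---|---|---|---|---|
| equal | any | 1.000 | 5.0% | 80.0% |
| 30% vs 15% | 0.7 | 0.953 | 8.5% | 86.7% |
| 40% vs 15% | 0.6 | 0.894 | 15.6% | 93.0% |
| 15% vs 30% | 0.7 | 1.049 | 2.8% | 71.6% |
| 15% vs 40% | 0.6 | 1.119 | 1.1% | 58.3% |

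The higher power in the second and third rows comes from the same bias and is not a gain.

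Other assumptions widen the range. With h = 0.8 and 40% vs 30%, false non-inferiority is 6.4%, or power is 76.5% if the shares are reversed. With h = 0.6 and 50% vs 20%, the figures are 19.5% and 52.2%.

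These calculations ignore partial adjustment through GTV and KPS, and they use the unweighted design SE. If weighting inflated the variance by an assumed 1.2 to 1.5, 15.6% would become 14.3% to 13.0%, and 8.5% would become 8.1% to 7.7%.

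**The case against.** **The document does not show that re-resection confounds.** That needs both a survival effect and an imbalance, and neither is given. The two adjusted comparisons of ReRT schedules in section 1.1 list covariates such as KPS, time interval, PTV and initial WHO grade, but not re-resection. This stands in full as a limit on size and direction. It does not justify leaving a permitted pre-treatment intervention out of the adjustment for a non-randomized comparison.

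**GTV is not wrong.** A reader might infer that surgery distorts the GTV covariate, or that balancing on GTV makes matters worse. The documents do not support this. GTV is the enhancing volume at time zero, a proper baseline measure of disease burden, and nothing shows that adjusting for it does harm. It is incomplete as a stand-in for surgery, no more. The requirement of contrast enhancement in section 4.2 may also keep out some fully resected patients, which narrows the gap.

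**The variable may not be at hand.** A reader might infer that eligibility already requires a re-resection date for every patient. It requires only that a re-resection within 3 weeks be ruled out. The last re-resection also need not be one for the current recurrence, and the protocol does not say that the registry holds that item. This stands and affects the cost of the fix.

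**This could be left to the SAP.** Section 8.1 allows minor revisions and requires a final plan before recruitment ends. That keeps the correction possible, but section 8.1.1 already names the covariates, and the list as stated omits an allowed co-intervention. Other items, such as number of recurrences, baseline dexamethasone and IDH status, are also outside the propensity list, and the document cannot rank them. Re-resection is singled out because it is itself a salvage treatment allowed before time zero.

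**Conclusion.** The point holds as an omission from the stated adjustment set. Re-resection before ReRT is allowed, its recent use is checked in both arms, and it appears in no matching, propensity or exploratory list. Any difference between arms would reach the primary hazard ratio, offset only in part by GTV and KPS.

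The size and direction are unknown. Under the two main assumed scenarios, false non-inferiority at a true HR of 1.4 rises from 5% to about 8.5% or 15.6%. With the shares reversed it falls to about 2.8% or 1.1%, and power at HR 0.90 drops from 80% to about 72% or 58%. Equal shares, or no effect of re-resection, give no bias. A reader might infer that the plan favors the experimental arm; without re-resection rates that cannot be said. The change is worth making because it is small and protects the primary comparison, not because a bias has been shown.

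**What to change.** In section 8.1.1, add re-resection for the current recurrence before ReRT (yes/no) to the propensity model used for OS and PFS. Report its frequency by arm and its balance before and after weighting. State that GTV is the enhancing volume at ReRT, postoperative where surgery took place, in both arms.

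The cost is one more term in the logistic model. The sample size stays at 165 and no clinical rule changes. Before the SAP is final, the sponsor should confirm that the item can be retrieved from the retro-RISinG registry for the 83 registry controls, and report any missing values. If retrieval is poor, that should be stated as a limitation of the comparison.
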